### Provisions for post-trial care {30}

Planned treatment after clinical trial end: The investigator will continue to observe all subjects (also withdrawals) because of intolerable AEs/ SAEs until the findings have been resolved or became stable. For injuries caused to participating persons and arising out of this research performed in accordance with the protocol and applicable law and professional standards, an insurance is in place.

## Outcomes {12}

### Primary efficacy endpoint

Occurrence of postoperative SSI within 30 days after surgery (POD30). SSI is the most common and relevant complication after OS and may be associated with subject’s discomfort, prolonged hospital stay, increased postoperative morbidity, and higher costs of medical care. Thus, SSI has been evaluated in different previous trials [4]. Definition and determination of SSI are based on the standardised used criteria of the American “Center for Disease Control and Prevention” (CDC), which correspond to the recommendations of the “European Center for Disease Prevention and Control (ECDC) as well as the recently introduced German KISS-definitions (Krankenhaus-Infektions-Surveillance-System) of the “National reference centre for surveillance of nosocomial infections - Robert Koch Institut” [17–19]. Therefore, those criteria are the worldwide absolute, undisputed standard in the assessment of postoperative SSI. All of those criteria were introduced to guarantee international comparability of surveillance data and have been used in a plethora of international recognised studies [4, 15, 20]. Just recently, the new German KISS-definitions (which are in form and content based on the CDC criteria) for the evaluation and prevention of SSI have been published [17, 18].

### Secondary endpoints

Deep incisional and/or organ or space SSI as defined by CDC/KISS [17, 21] 30 (POD30) to 90 days after surgery (POD90). As an implant is used, a deep incisional or organ and space SSI may occur within 90 days after surgery according to CDC/KISS criteria [17, 21].Systemic infections, defined as a systemic inflammatory response syndrome associated with a postoperative SSI consecutive to OS. Systemic infections might be associated with postoperative SSI. However, since OS is a scheduled procedure, and surgeons do not perform it in patients at high risk of infection, systemic infection is very unlikely to occur.Length of hospital stay (LOS), defined as the number of days from OS to the day of discharge. LOS is an important subject-oriented outcome and can be directly or indirectly influenced by SSI.Health-related quality of life (HRQoL), measured by SF-36 and OHIP-G-14 [22–24]. HRQoL is an important patient-oriented outcome and can be directly or indirectly influenced by SSI. Furthermore, there might be connections between subjects’ expectations regarding the postoperative AP and their QoL independent from an SSI. Antibiotics are often prescribed due to subjects’ expectations in order to enhance their QoL.Non-severe medication related adverse events (AE), defined as mild diarrhoea or skin rash due to antibiotic administrations. Ampicillin/Sulbactam antibiotic are well established, tested and tolerated antibiotics. However, diarrhoea and skin rashes are reported. Adverse effects associated with antibiotic intake are of great interest when evaluating the elective/prophylactic use of antibiotics.

### Participant timeline {13}

Table 1 shows the clinical trial schedule. The clinical trial period for an individual subject consists of a 4-day treatment period and a follow-up phase until POD90.

**Table 1 Tab1:** Clinical trial schedule

Visit no.		V1	V2			V3		V4	V5	V6	V7	V8
Phase		Screening/baseline		Treatment					Follow up			
Relative time point	Day	D-28 to D-1 Pre-surgery visit/hospital admission^a^	D0		POD1	POD2	POD3	POD4	POD 10 ± 3 days	POD 30 ± 3 days	POD 60 ± 3 days	POD 90 ± 3 days
			Pre-OS	Pos-OS								
Procedure												
Inclusion/ exclusion criteria	C	●										
Written informed consent	C	●										
Medical history, demography	R	^e^●										
Randomisation	C	^b^●										
Surgery			●									
^d^IMP administration	C			●	●	●	●	●				
Examination of mouth cavity	R	^e^●										
Mouth hygiene	R	●				●		●	●	●	●	●
^f^SSI	R					●		●	●	●	●	●
^g^Pregnancy test	C	^c^●										
^h^Blood tests: CRP, WBC	R	^c^●						●		●		
HRQoL:SF-36, OHIP-G-14	C	●						●		●		●
^i^AE	R			●	●	●	●	●	●	●	●	●
^j^Concomitant medication	R	●		●	●	●	●	●	●	●	●	●
^k^Postoperative pain medication	R			●	●	●	●	●	●	●		
Smoking and/or alcohol consumption	R	●				●	●	●	●	●	●	●

*R* regular or *C* clinical trial specific examination; *POD* postoperative day; *OS* orthognathic surgery; *V* visit

^a^Routine pre-surgery information visit approx. 3–4 weeks before OS; routine hospital admission: D-1

^b^Randomisation: D-1 or earlier when subject eligibility confirmed and IC obtained

^c^Lab tests at hospital admission D-1

^d^IMP administration: Total of 12 doses will be administered during treatment phase (D0–POD4) over a period of 96 h

^e^Pathological findings detected prior to the 1st administration of IMP are to be documented as medical history, thereafter as adverse events

^f^SSI: post-op. evaluation of mouth cavity for signs and symptoms for SSI

^g^In females of child-bearing potential; performed in blood (HCG) or urine

^h^Blood tests: C-reactive protein (CRP) and WBC count. If SSI is diagnosed independent of trial visits, an additional blood sample is taken

^i^AE/SAE: adverse/serious adverse events. Pathological findings detected at/after the first administration of IMP are to be documented as AE/SAE

^j^Concomitant medication: prior concomitant medication (inclusive pre-operative medication, exclusive intraoperative medication)

^k^Postoperative pain medication as needed till POD30 to be documented

### Sample size {14}

The sample size calculation is based on the primary efficacy endpoint “Occurrence of SSI within thirty days after surgery (V4)”. A recent meta-analysis [1] reported a pooled risk ratio of 0.42 (95% confidence interval: [0.24; 0.74]) for the comparison of long-term (before or during surgery and longer than one day after surgery) versus short-term (before or during surgery and/or during the same day) antibiotic prophylaxis. Furthermore, pooled event rates of 7.1% for long-term and 16.8% for short-term antibiotic prophylaxis were observed, yielding a difference of 9.7%. Thus, for both the AP and no AP group, an infection rate of 7.1% is expected, as the assumption of equal rates is the standard approach for a power calculation in non-inferiority trials. If the rate in the no AP group is at most 4% higher than the rate in the AP group, this will be considered as clinically irrelevant since possible SSI might have an increase in clinically manageable morbidity, however, no life-threatening consequences for subjects.

Based on these assumptions, a total of *n* = 1346 subjects (673 per group) are required to demonstrate non-inferiority at a margin of *δ* = 4% for no AP as compared to AP applying the Farrington-Manning test at a one-sided significance level of *α* = 2.5% with a power of 1-β = 80% (calculations performed with ADDPLAN v6.1). The adjustment for the factor centre using a Mantel-Haenszel type test is expected to yield an additional increase in power. To account for a drop-out-rate of 5%, a total of *n* = 1420 subjects (710 per group) will be randomised.

The potential problem of missing values for the primary outcome due to loss to follow up or premature withdrawal from the study before the measurement of the primary endpoint will be partly resolved in the confirmatory analysis by application of a pre-defined imputation strategy (see the “Statistical methods” section).

### Recruitment {15}

The clinical trial will be conducted on a multicentre basis. Recruitment and treatment will take place at 14 centres. We calculated that 1420 subjects are being assigned for this trial within a recruitment period of 39 months resulting in approx. 570 subjects per year. In order to prove the feasibility of recruitment, we screened the DRG flat-rate catalogue of the German federal statistical office [7], the DRG index benchmarking reports of the university departments for oral and maxillofacial surgery in Germany as well as the results of the QB-analyser [25]. Justified on the department’s performance, invitation to participate was sent to the eligible centres. The coordinating centre at Heidelberg University conducts more than 200 OS per year, of which approximately 150 will are estimated to meet the inclusion criteria and agree to participate in the trial. With a major percentage of all OS performed on German Universities, the applicants will be able to contribute a large share of the necessary enrolment. Thirteen other centres with great expertise in OS, and thereby fulfilling the criterion for participation, have signed agreement to participate. According to each centre’s declaration of commitment, recruitment of 1420 subjects is expected to be feasible within 39 months. According to our experience, since all surgical interventions are elective on usually young and healthy subjects, there is a motivation to take part in trials aiming to reduce antibiotic intake.

## Assignment of interventions: allocation

### Sequence generation {16a}

To achieve comparable intervention groups, subjects will be allocated in a concealed fashion in a 1:1 ratio by means of randomisation which will be performed by delegated staff members of the local pharmacy using a centralised web-based tool (www.randomizer.at). Randomisation will be performed stratified by location (bimaxillary or mandibular only osteotomy) and centre. Block randomisation will be performed to achieve in total equal group sizes per centre and location.

### Concealment mechanism {16b}

Details of the randomisation scheme such as the block length are specified by the trial biometrician and only provided in an external document accessible to the Institute of Medical Biometry and Informatics (IMBI) only to minimise selection bias. The block length will not be disclosed to any other personnel involved in the trial, thus providing allocation concealment. The randomisation numbers will be allocated sequentially in the order in which the subjects are enrolled.

### Implementation {16c}

In each clinical trial site, all subjects who enter the screening period for the trial will receive a unique Subject ID before any trial-related procedure is performed. The Subject ID (Screening Number) will be assigned by the clinical trial site as a consecutive number. This Screening Number will be used to identify the subject throughout the clinical trial and must be used on all trial documentation related to the patient. Clinical sites must complete the appropriate pages of the electronic case report form (eCRF) for all subjects randomised, even if the subject is not treated in the study. Subjects who fulfil the enrolment criteria—which will be checked by the clinical site—will be randomised by the pharmacy or a delegated staff member not involved in the assessment of the subject. The allocation sequence is determined via the employed online randomisation tool based on the specifications provided by the trial biometrician. The Screening Number will be entered as Subject-ID into the randomisation tool which will allocate the Randomisation Number sequentially in the order in which the subjects have been enrolled. Both the Screening Number and the Randomisation Number will be recorded on the individually prepared infusion bag by the pharmacist or a delegated site member not involved in the assessment of the subject. Every site is obliged to strictly adhere to this randomisation procedure. The correct assignment will also be verified by the clinical monitor at each site.

## Assignment of interventions: blinding

### Who will be blinded {17a}

Double blinding of investigators and subjects will be performed in order to avoid bias due to differences in performance and perception. In addition to the clinical trial medication prepared by the local pharmacy after randomisation of each patient, a sealed envelope (emergency envelope) will be forwarded to the investigator via the local pharmacy, one for each randomisation number. The envelope contains information on the subject’s clinical trial medication and is to be opened only under circumstances in which it is medically imperative to know what the subject is receiving. The envelopes are not to be opened by the investigator at the end of the clinical trial. All envelopes will be collected by the responsible monitor at the end of the clinical trial.

### Procedure for unblinding if needed {17b}

Only delegated members of the local pharmacy (or other staff member not involved in the subjects’ treatment and assessment as delegated by the investigator, ensuring that study staff will at all times remain blinded regarding subject’s treatment) responsible for performing randomisation at the site will have access to the randomisation tool. If it is medically imperative to know what clinical trial medication the subject is receiving, the investigator or authorised person should open the emergency envelope. The investigator or the authorised person who breaks the blind must record the date and the reasons for doing so in the eCRF, in the subject’s medical record and on the emergency envelope. Whenever possible, the coordinating investigator (LKP) should be contacted before the blind is broken.

## Data collection and management

### Plans for assessment and collection of outcomes {18a}

All protocol-required information collected during the trial must be entered by the investigator, or designated representative, in the eCRF. The investigator, or designated representative, should complete the eCRF pages as soon as possible after information is collected, preferably on the same day that a trial subject is seen for an examination, treatment, or any other trial procedure. Any outstanding entries must be completed immediately after the final examination. An explanation should be given for all missing data. The completed eCRF must be reviewed and signed by the investigator named in the trial protocol or by a designated sub-investigator.

### Plans to promote participant retention and complete follow-up {18b}

The patients will receive extensive information about the study set-up and requirements during the recruitment. The importance of completion of the follow up will be stressed. However, the frequency of visits is consistent with the routine clinical care of this subject group. All measurement time points chosen are part of the standardised follow-up protocols and standard visits after OS interventions. The scheduled investigations are consistent with routine clinical care and partly correspond to study-related procedures. Since the intervention always is a combination of surgery and orthodontics, with a succeeding period of therapy by the orthodontics up to 2 years after surgery, compliance is very high in OS patients and loss of follow-up is expected to be low.

### Data management {19}

The IMBI is responsible for the data management within the trial. An eCRF will be used for data collection. To assure a safe and secure environment for data acquired, data transmission is encrypted with secure socket layer (SSL) technology. Only authorised users are able to enter or edit data, the access is restricted to data of the subjects in the respective centre. All changes to data are logged with a computerised timestamp in an audit trail. All data will be pseudonymised. To guarantee high data quality, data validation rules will be defined in a data validation plan. Completeness, validity and plausibility of data will be checked in time of data entry (edit-checks) and using validating programs, which will generate queries. If no further corrections are to be made in the database, eCRF data will be locked. Data will finally be downloaded and used for statistical analysis. All data management procedures will be conducted according to written defined standard operating procedures (SOPs) of the IMBI that guarantee an efficient conduct complying with good clinical practice (GCP). At the end of the study, the data will be transformed into different data formats for archiving and to ensure that it can be re-used.

### Confidentiality {27}

The data obtained in the course of the clinical trial will be treated pursuant to the EU General Data Protection Regulation (GDPR) (national regulatory requirements, e.g. (Bundesdatenschutzgesetz, BDSG).

During the clinical trial, subjects will be identified solely by means of their individual identification code (screening number, randomisation number). Clinical trial data stored on a computer will be stored in accordance with local data protection law and will be handled in strictest confidence. Distribution of these data to unauthorised persons has to be prevented strictly. The appropriate regulations of local data legislation will be fulfilled in its entirety.

The subject consents in writing to release the investigator from his/her professional discretion in so far as to allow inspection of original data for monitoring purposes by health authorities and authorised persons (inspectors, clinical monitors, auditors). Authorised persons (inspectors, clinical monitors, auditors) may inspect the subject-related data collected during the clinical trial ensuring compliance with the effective data protection law.

The investigator will maintain a subject identification list (screening numbers with the corresponding subject names) to enable records to be identified. Subjects who did not consent to circulate their pseudonymised data will not be included into the clinical trial.

This protocol, the eCRFs and other clinical trial-related documents and material must be handled with strict confidentiality and not be disclosed to third parties except with the express prior consent of Sponsor. In particular, it must be ensured that the clinical trial medication is kept out of reach of third parties. Staffs of the investigators involved in this clinical trial are also bound by this agreement.

### Plans for collection, laboratory evaluation and storage of biological specimens for genetic or molecular analysis in this trial/future use {33}

There will be no collection of biologic specimens for further analysis in the future in this trial.

## Statistical methods

### Statistical methods for primary and secondary outcomes {20a}

#### Analysis of primary endpoint

Non-inferiority of no AP vs. AP will be assessed using the test according to Mantel and Haenszel extended to the non-inferiority case [26, 27] which allows adjustment for the factor centre. The one-sided significance level is set to 2.5%. The hypotheses to be assessed in the primary efficacy analysis are as follows: *H*_0_ : *p*_*no AP*_ − *p*_*AP*_ ≥ *δ* and *H*_1_ : *p*_*no AP*_ − *p*_*AP*_ < *δ*, where *δ* = 4% represents the chosen non-inferiority margin and *p*_*no AP*_ / *p*_*AP*_ denote the SSI rate at Visit 4 (POD30) in the no AP and AP group, respectively.

The primary efficacy analysis will be based on the modified ITT set including all randomised subjects who postoperatively received at least one dose of placebo or AP, reflecting the recommendations given in guidelines (e.g. [28]). Furthermore, in [29], it was demonstrated that for the particular setting of antibiotic non-inferiority trials, the ITT and the PP set, excluding subjects with major protocol violations, yield almost identical results. Thus, modified ITT should be preferred over PP as the primary efficacy set here. Additionally, an evaluation of the primary outcome will be performed in the PP set, in accordance to [30] where the importance of the PP set in non-inferiority trials was emphasised. Before database closure, the assignment of each subject to the modified ITT and the PP population are defined in the statistical analysis plan.

Sensitivity analyses will be performed by applying alternative methods dealing with missing data such as, e.g. complete case analysis and replacement by ICA-r [31]. Besides the adjustment for centre which is included into the primary analysis, a generalised linear model with identity link and binomial error will additionally be fitted for a comparison of the SSI rates between the groups adjusting for location and centre. Furthermore, the primary endpoint will be evaluated by the Farrington-Manning test [32] for the unadjusted non-inferiority assessment of rate differences not considering any potential confounders.

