#### Analysis of secondary endpoints

All secondary outcomes will be evaluated descriptively. Analyses of secondary endpoints will be conducted based on the m-ITT set, with additional sensitivity analyses based on the PP set.

The secondary endpoints “Deep incisional and/or organ or space SSI within 90 days after surgery” and the secondary endpoint “systemic infections” will be evaluated by means of a logistic mixed regression model using for the fixed factors treatment group and location, as well as the random factor centre. Odds ratios will be given with 95% confidence intervals together with descriptive *p* values.

The secondary endpoint LOS will be assessed using Kaplan-Meier estimates for each treatment group. A Cox regression frailty model with the fixed factors treatment group and location and the random factor centre will be fitted. A hazard ratio for the factor treatment group will be given with a 95% confidence interval together with a descriptive *p* value.

HRQoL at follow-up will be analysed using a linear mixed model for repeated measurements, taking into account the HRQoL baseline value, treatment group, and location as fixed factors, centre as random factor, and time as repeated factor using an unstructured covariance matrix. 95% confidence for the mean difference between treatment groups will be given with descriptive *p* values. No imputation of missing data will be done for secondary endpoints.

Furthermore, the treatment effect will be assessed descriptively within several subgroups of interest to identify potential prognostic and predictive factors.

The safety analysis includes calculation of frequencies and rates of adverse and serious adverse events together with 95% Wilson-type confidence intervals. Safety analysis will be based on the safety set comprising all subjects of the m-ITT set who postoperatively received at least one dose of placebo or postoperative AP and will allocate the subjects to the treatment they actually received, regardless of randomisation.

Statistical analysis is based on the International Conference on Harmonization (ICH) Guidelines “Structure and Content of Clinical Study Reports” and “Statistical Principles for Clinical Trials” [28]. All statistical procedures are done according to the current standard operating procedures (SOPs) of the Institute of Medical Biometry and Informatics, University of Heidelberg (IMBI).

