### Methods in analysis to handle protocol non-adherence and any statistical methods to handle missing data {20c}

Missing data for the primary outcome variable due to loss to follow-up or early withdrawal before measurement of the primary endpoint will be replaced by using multiple imputation [33], which takes the covariates treatment group, location (bimaxillary or mandibular osteotomy), and centre into account by application of the fully conditional specification method [29]. This will be realised using the option “FCS” of the SAS “MI” procedure which is implemented in SAS 9.4.

Post-randomisation events will be handled as follows in accordance with the estimands framework. Subjects not undergoing surgery or not receiving at least one dose of postoperative AP or placebo will be excluded, which corresponds to a modified intention-to-treat principle and a principal stratum strategy, as not undergoing surgery or not receiving at least one dose of study treatment is independent of treatment allocation due to the blinded character of the trial. Patients who are lost to follow up or prematurely withdraw their consent before measurement of the primary endpoint will be considered as missing and multiple imputation will be used to impute the primary outcome of these patients, corresponding to a hypothetical strategy. Besides these events, other post-randomisation events will not be considered, thus reflecting a treatment policy approach, which means that the effect of randomised treatment is estimated irrespectively of other post-randomisation events not captured in the primary endpoint definition.

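### The confirmatory Mantel-Haenszel test is stratified by centre only although randomisation is stratified by location and centre; this costs a little precision and is cheap to align

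*Protocol article*

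**What the plan says.** Under Sequence generation {16a}, the design is stated as follows: "Randomisation will be performed stratified by location (bimaxillary or mandibular only osteotomy) and centre". Blocks are used within these strata.

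Under Analysis of primary endpoint, the confirmatory test is a Mantel-Haenszel test "extended to the non-inferiority case [26, 27] which allows adjustment for the factor centre". The same section confirms that centre is the factor handled in the primary analysis and sets a supplementary identity-link binomial model apart from it, whose stated purpose is a "comparison of the SSI rates between the groups adjusting for location and centre". An unadjusted Farrington-Manning test is also listed. The Sample size {14} section likewise names centre alone: "The adjustment for the factor centre using a Mantel-Haenszel type test is expected to yield an additional increase in power".

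Location appears elsewhere in the plan. The multiple imputation of missing primary outcomes uses a model "which takes the covariates treatment group, location (bimaxillary or mandibular osteotomy), and centre into account" (section {20c}). Deep or organ/space infection and systemic infection are analysed by a "logistic mixed regression model using for the fixed factors treatment group and location, as well as the random factor centre". The models for length of stay and quality of life also contain location.

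**The concern.** The usual principle is to analyse as randomised. Blocking within centre and location forces the arms to be balanced on location, so any difference in infection risk between the two procedures no longer adds to the sampling variability of the estimated difference. A variance estimate that does not condition on location still counts that component. The standard error is then too large, and the upper confidence limit sits slightly too far out.

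The sample size section expects adjustment for centre to add power. The same reasoning applies to the other randomisation factor, yet the confirmatory test leaves it out while the imputation model and the regression models for the secondary endpoints include it. At stake is a little precision, and which of three pre-specified results (centre-adjusted, location-and-centre-adjusted, unadjusted) counts as confirmatory if the upper limit falls close to 4 points.

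**Working it through.** **Inputs from the article.** SSI rate 7.1% in both arms; margin 4 points on the risk difference; one-sided alpha 2.5%; power 80%; 1:1 allocation; 14 centres; 673 per group (1346 in total), 1420 randomised.

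**Inputs the article does not give (assumed).** Bimaxillary share 50 to 85%; ratio of SSI rates between locations 1 to 3, with the overall rate held at 7.1%; between-centre standard deviation 2 points; block length 4 (deliberately not disclosed in the article).

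**Step 1: reproduce the planned sample size.** Farrington-Manning, with rates restricted to a difference of 0.04: 0.0959 and 0.0559.

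- Variance term under the null: 0.0959 × 0.9041 + 0.0559 × 0.9441 = 0.1394, square root 0.3734.
- Variance term under the alternative: 2 × 0.071 × 0.929 = 0.1319, square root 0.3632.
- n per arm = [(1.960 × 0.3734 + 0.8416 × 0.3632) / 0.04]² = 672.8, so 673 per arm and 1346 in total.

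This matches the article. The calculation uses no stratification, so adding location to the strata cannot change it.

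**Step 2: size of the effect at the far end of the assumed range.** Take a 50% share and a rate ratio of 3, so rates of 10.65% and 3.55%.

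- Total binomial variance: 0.071 × 0.929 = 0.06596.
- Part due to location: 0.5 × 0.5 × (0.1065 − 0.0355)² = 0.00126, or 1.9% of the total.
- Standard error ignoring location: √(2 × 0.06596 / 673) = 0.01400.
- Standard error within location: √(2 × 0.06470 / 673) = 0.01387.
- Shift in the upper limit: 1.96 × (0.01400 − 0.01387) ≈ 0.00026, or 0.026 percentage points against a margin of 4.
- Power at a true difference of zero. Blocking has already reduced the real sampling variability to 0.01387, so only the estimated standard error changes: Φ[(0.04 − 1.96 × 0.01400) / 0.01387] = 81.7% without location and Φ[(0.04 − 1.96 × 0.01387) / 0.01387] = 82.2% with it. The gain is 0.5 points.

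**Step 3: simulation.** 40,000 trials per setting; 1346 subjects with complete outcomes; 14 centres, one of them large; blocks of 4 within centre and location; Mantel-Haenszel risk difference with the Sato variance.

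| Bimaxillary share | Rate ratio | Power, centre strata | Power, centre × location strata |
|---|---|---|---|
| 50% | 1 | 81.5% | 81.5% |
| 50% | 2 | 81.8% | 82.0% |
| 50% | 3 | 81.8% | 82.2% |
| 70% | 2 | 81.6% | 81.8% |
| 70% | 3 | 82.0% | 82.2% |
| 85% | 3 | 81.8% | 81.9% |

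Over all twelve settings, power is 81.5 to 82.0% with centre strata and 81.5 to 82.2% with centre × location strata. The largest gain is about 0.5 points, in agreement with Step 2. At a true difference of 4 points, the rejection rate is 2.5 to 2.7% under either stratification. Bias of the estimated difference is about zero under either.

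**Step 4: stratum sizes.** 14 × 2 = 28 strata, and 1346 / 28 ≈ 48 subjects on average. Centres will be uneven. The Recruitment section expects about 150 participants at the coordinating centre; read as a yearly figure over 39 months, that is 150 × 3.25 ≈ 488. The other 13 centres would then average (1420 − 488) / 13 ≈ 72 each. With 15 to 30% mandibular-only cases, their mandibular-only strata would hold about 11 to 22 subjects and, at 7.1%, about 0.8 to 1.5 infections over both arms.

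**The case against.** The strongest reply is that centre-only adjustment is a consistent, stated choice and does no harm. The sample size and analysis sections both name centre alone, and nothing in the article promises a confirmatory test adjusted for location. The article condenses a fuller protocol, so a missing rationale is not a fault in itself. An over-wide limit is also the safe direction in a non-inferiority trial. All of this stands, and it sets the grade of the point. It does not remove the mismatch between the randomisation strata and the analysis strata, which the article fixes explicitly.

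A reader might infer that the primary analysis ignores location altogether. It does not: the imputation feeding the confirmatory test conditions on location, and a pre-specified model on the risk-difference scale adjusts for it. That model is supplementary, however, and identity-link binomial fits with many centre terms and about 96 expected events (1346 × 0.071) can have trouble converging.

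A reader might also infer that location was chosen as a stratum because infection risk differs between the procedures. The article gives only the general aim of comparable groups, so any risk difference is an assumption here.

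Finally, the change is not entirely without cost. Small mandibular-only strata will occur, and a stratum with only one arm contributes nothing to a Mantel-Haenszel estimate. That part of the objection stands and shapes the fix.

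**Conclusion.** The mismatch is real and minor. Leaving location out of the confirmatory test widens the confidence limit very slightly and gives up about 0 to 0.5 points of power, for assumed rate ratios of 1 to 3 and bimaxillary shares of 50 to 85%. If the two procedures carry the same risk, nothing is lost.

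The documents do not support reading this as a threat to validity. Allocation is balanced within location, so the risk difference is unbiased. The simulated rejection rate at the margin is 2.5 to 2.7% with or without location in the strata, so the slight excess over 2.5% does not come from the omission. Nor is the trial underpowered on this account: simulated power with centre-only strata is already at least 81.5%.

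A larger power gain would need a rate contrast beyond the assumed range. Treating the variance saving as if it were extra subjects would also overstate the gain, because the blocking has already removed that variability from the estimate and only the estimated standard error changes.

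**What to change.** Define the confirmatory analysis as a Mantel-Haenszel risk difference tested against the 4-point margin, stratified by centre × location as randomised (28 strata). Pre-specify, before unblinding, a rule for one-arm or very small strata, for example pooling small centres within location. Keep the centre-only Mantel-Haenszel test and the unadjusted Farrington-Manning test as sensitivity analyses, and change the remark on adjustment in the sample size section to name both factors.

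If the sponsor prefers to keep centre alone, a sentence giving the reason would settle the point.

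The cost is a line or two in the protocol and the SAP. No additional data are needed, and 1346 evaluable and 1420 randomised subjects remain as planned.
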